# Discontinuation criteria for individual subjects

　　The principal investigator or sub-investigator will discontinue the study for subjects who are unable to continue the study due to the following reasons, and will take appropriate treatment based on the benefit to the subject. In addition, scheduled surveys/inspections shall be conducted as soon as possible to make a decision (Except in cases where it cannot be conducted due to withdrawal of consent, etc.). If consent is withdrawn after the administration of the study food has begun, it should be made as clear as possible whether the withdrawal is due to ineffectiveness of the study food or an adverse event, or whether it is due to an accidental event (e.g., change of location), and it should be recorded so that it can be used as a reference for the selection of the case for efficacy and safety evaluation. The investigator or sub-investigator should record the date of discontinuation, reason for discontinuation, and comments in the case report form. After discontinuation of the study, if any of the following items 4)-6), 10) are found, hematological and biochemical tests should be performed to confirm safety. In addition, medical examinations will be conducted as deemed necessary by the physician for each symptom. Patients will be followed up for one year after treatment as deemed necessary by the physician according to the examination results. In particular, if the study is discontinued due to the occurrence of an adverse event, follow-up will be conducted until the patient recovers to the original state as much as possible.

1. When the subject declines to participate in the study or withdraws consent
2. Other reasons depending on the subject (e.g., too busy, hospital transfer, relocation)
3. If it is found that the eligibility is not satisfied after registration
4. When it is judged inadvisable to continue administration of the test food due to worsening of the primary disease.
5. If it is difficult to continue the study due to exacerbation of complications
6. If it is difficult to continue the study due to adverse events
7. When pregnancy is detected
8. If the entire study is discontinued
9. If the physician deems it appropriate to stop the study for any other reason.

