　Subcontractor name: LSI Medience Co.Ltd.

・QOL：SF－36

　　・ADL：mHAQ

・Disease activity：DAS28-ESR・DAS28-CRP・SDAI・CDAI

・Sonographic examination of joints：sonographic examination of synovitis in 7 joints on the side with stronger symptom at baseline (unchanged during the observation period) (2nd and 3rd metacarpophalangeal (MP) joints, 2nd and 3rd proximal interphalangeal (PIP) joints, wrist, and 2nd and 5th metatarsophalangeal (MTP) joints) using both grayscale (GS) (grade 0–3) and power-Doppler (PD) scale (grade 0–3)

Timetable

| Item | pre-  observation | Start administering the test foods | Administration period | End of test food administration | post-  observation |
| --- | --- | --- | --- | --- | --- |
| Period | Before  1-4 weeks | 0 week | After 12 weeks  (±7day) | After 24 weeks  (±7day) | After 12 weeks |
| Medical Examination | 1 | 2 | 3 | 4 | 5 |
| Consent obtain | ○ |  |  |  |  |
| Check patient background | ○ |  |  |  |  |
| Test food administration |  |  |  |  |  |
| Subjective symptoms and other findings | ○ | ○ | ● | ● | ● |
| Observation of adverse events^a^ |  |  | ● | ● | ● |
| Anthropometry^b^ |  | ○ |  | ● |  |
| Blood pressure and pulse measurement |  | ○ | ● | ● | ● |
| Hematological examination |  | ○ | ● | ● | ● |
| Blood Biochemistry Test |  | ○ | ● | ● | ● |
| Sonographic examination of joints |  | ○ | ● | ● | ● |
| QOL assessment |  | ○ |  | ● |  |
| Disease activity assessment^c^ | ○ | ○ | ● | ● | ● |

　Items marked with an asterisk ○ are items to be performed before administration of the test food, and items marked with an ● are items to be performed after administration of the test food.

a: Adverse events are all events that are undesirable, such as side effects, regardless of whether they are causally related to the test food.

b: Measure height, weight, and abdominal circumference as anthropometry.

c: Evaluate DAS28-ESR, DAS28-CRP, SDAI, and CDAI for disease activity.

Blood tests should be performed under fasting conditions to rule out the effects of diet.

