# Evaluation items

## Primary endpoints

　The primary endpoint of this study is the change in disease activity DAS28-ESR at 24 weeks after the start of the test food intake.

【Evidence of setting】

　In this study, we will investigate the suppressive effect of Brazilian propolis on the disease activity of RA. The above item of disease activity is the gold standard not only for ACR/EULAR but also for the assessment of disease activity in RA worldwide.

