# Statistics Analysis

## Data handling

When compiling data for observation and inspection items specified in the plan by time period, data for inspection items performed on days or at times outside the acceptable range shall be treated as missing. For missing values, LOCF completes the values when the main analysis is performed.

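### Section 9 does not separate stopping the test food from leaving the study, so the week-24 DAS28-ESR is not guaranteed for patients stopped because their RA worsened

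*Protocol*

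**What the plan says.** Section 9 (Discontinuation criteria for individual subjects) has one list of reasons. Its lead sentence says the investigator "will discontinue the study for subjects who are unable to continue the study due to the following reasons". On care at that point, the same sentence adds that he or she "will take appropriate treatment based on the benefit to the subject". Item 4 is "When it is judged inadvisable to continue administration of the test food due to worsening of the primary disease". Item 3 is "If it is found that the eligibility is not satisfied after registration".

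After discontinuation, section 9 says "scheduled surveys/inspections shall be conducted as soon as possible to make a decision". It adds safety blood tests for a subset of reasons that includes item 4, and up to a year of follow-up if the physician thinks it necessary. An adverse event that caused discontinuation is followed towards recovery. DAS28-ESR is one of the scheduled items (section 8, timetable note: "c: Evaluate DAS28-ESR, DAS28-CRP, SDAI, and CDAI for disease activity"), so the examination at discontinuation can include it.

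The primary endpoint (section 12.1) is "the change in disease activity DAS28-ESR at 24 weeks after the start of the test food intake". Under section 14.1, "data for inspection items performed on days or at times outside the acceptable range shall be treated as missing", and the main analysis fills missing values by LOCF. Section 14.2 adds a mixed-effects model as a supplementary check on LOCF.

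**The concern.** Stopping the test food and leaving the study are different events. A patient can come off the tablets and still attend at week 24. Section 9 treats the first as a cause of the second and then does not ask for the later visit.

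Under item 4 the trigger is worsening of RA, and the endpoint is RA disease activity. Any loss of the week-24 value is therefore related to the outcome, and it may differ between arms if the test food works, or if it harms. The main analysis would then rest partly on carried values that describe another time and another treatment situation. The choice of analysis method can soften this but cannot stand in for an observation at week 24.

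Item 3 is a smaller matter. A randomised patient's outcome may be lost there too, but nothing suggests a link with the outcome.

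**Working it through.** **1. Does the text end follow-up?** Within the section 9 list, items 5 and 6 are phrased as difficulty in continuing the study. Item 4 is phrased as inadvisability of continuing the test food. All of them fall under the same lead sentence, which ends study participation. So under item 4 a decision about the food triggers exit from the study.

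**2. Does another passage restore the week-24 value?**
- Section 7.3 gives a follow-up of up to 40 weeks for all patients. This is a maximum duration and gives no instruction for discontinued patients.
- Section 7.5 lets RA medication change when the disease is not controlled. This keeps some worsening patients in the study, but it does not cover those who come off the food.
- Sections 5.1, 18.2 and 18.3 describe three-monthly assessment and tests at the frequency of usual care. A DAS28-ESR near week 24 is therefore plausible, but it is not a required study value.
- Section 10.1 defines adverse events broadly enough that RA worsening could count as one, and section 9 would then follow the patient towards recovery. That follow-up names neither DAS28-ESR nor week 24.

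None of these requires the value.

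**3. What enters the main analysis?** There are two readings, because the acceptable range in section 14.1 is not spelled out beyond the ±7 days shown in the timetable for the week-12 and week-24 visits.
- If the discontinuation examination falls outside a window and is treated as missing, LOCF can carry a value from before the worsening.
- If it is kept, LOCF carries the worsened value, measured before the treatment given at discontinuation can act.

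The supplementary mixed model can use a recorded worsened value, for instance one found at the week-12 visit. The loss therefore need not be missing not at random. The model has no later data on these patients.

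**4. Scale from the plan.** Inputs from section 15.2: difference 0.5, SD 0.78, two-sided 5%, 80% power. n per group = 2 × (1.960 + 0.842)² × 0.78² / 0.5² = 38.2, rounded up to 39 (39.2 with the t distribution). The plan's 39 reproduces; 40 are to be enrolled. The standard error of the difference at 40 per group is 0.78 × √(2/40) = 0.17.

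**5. Illustration with assumed inputs.** The documents give no stop rate, so everything in this step is assumed. The shift in the propolis-minus-placebo difference is

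(propolis stop rate − placebo stop rate) × (carried value − actual week-24 value).

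Take gaps of 5 or 10 percentage points (2 or 4 of 40 patients) and a carried value 0.5 to 1.2 points away from the actual one:
- smallest: 0.05 × 0.5 = 0.025, or 5% of 0.5;
- largest: 0.10 × 1.2 = 0.12, or 24% of 0.5.

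If placebo patients stop more often, a carried value that is too low moves the result towards no effect, and one that is too high moves it towards benefit. If propolis patients stop more often, both signs reverse. With equal stopping and equal error the shift is zero. These figures are bounds only within the chosen inputs.

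**The case against.** The strongest reply is that little may be lost. Section 7.5 keeps many worsening patients in the study on changed medication, so item 4 is a residual group of unknown size. Visits are three-monthly, so worsening may often be recognised at the week-12 visit, inside its window, and be recorded. Usual care would often yield a later DAS28-ESR. The illustrated shift is below the standard error of 0.17. All of this stands, and it limits the weight of the point. It does not turn a possible value into a required one.

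Some stronger readings are tempting but are not supported:
- A reader might infer that the week-24 value is never collected. The protocol only fails to require it.
- A reader might infer that LOCF will favour propolis, or favour placebo. The sign depends on which arm stops more and on which value is carried, and neither is known.
- A reader might set these stops against the margin of 40 enrolled over 39 required. That does not follow: a patient who took the food and has one later efficacy assessment stays in the FAS with a carried value.
- A reader might call the value at discontinuation wrong in itself. It is wrong only for the question of week-24 status regardless of later treatment. The protocol does not say whether it asks that question or one about the period on the food.
- A reader might treat late-found ineligibility (item 3) as outcome-related. Nothing in the protocol says so, and section 6 checks eligibility before allocation, so such cases should be uncommon.

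**Conclusion.** The point holds in a limited form. As written, section 9 lets a decision to stop the food for RA worsening end study participation, and no other section then requires the week-24 DAS28-ESR. The primary outcome can therefore be missing for a reason tied to that outcome, with LOCF filling the gap and a mixed model that has nothing later to draw on.

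The number of such patients, and the size and direction of any bias, cannot be derived from the protocol. The illustrated 0.025 to 0.12 points rests wholly on assumed stop rates and carried-value errors, and it takes the actual week-24 status, on or off the food, as the target. This is a change worth making because it is cheap and guards the primary endpoint. It does not show that the planned result would be wrong.

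**What to change.** In section 9, separate two events: stopping the test food and leaving the study. State that a patient who stops the food for worsening, or who is later found ineligible, and who has not withdrawn consent to follow-up, keeps the scheduled DAS28-ESR and adverse-event assessments to week 36, with treatment changes recorded. In sections 14.1 and 14.2, state that an observed week-24 value is used instead of LOCF in the FAS analysis, whether the patient is on or off the food, and that non-adherence and ineligibility are handled in the PPS.

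The cost is amendment wording and a few extra study assessments at visits that are routine anyway (sections 5.1, 18.2 and 18.3). The main downside is that some week-24 values will be measured off the food or after rescue treatment, so the FAS result then describes outcome regardless of those changes. The protocol should say so. The change also supports the adverse-event endpoints that run to week 36 (section 12.2).

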# Handling of adverse events

## Response to subjects in an adverse event

　An "adverse event" is any unfavorable or unintended sign, symptom, or illness that occurs when a test food is administered, regardless of whether it is causally related to the test food.

When an adverse event is recognized, the principal investigator or sub-investigator should immediately take appropriate treatment and record it in the medical record and case report without any discrepancy.　In addition, subjects will be informed if the administration of the test food is discontinued or if treatment for adverse events becomes necessary. If it is necessary to identify the test food as an emergency evacuation, request the person in charge of test food allocation and coding through the principal investigator, etc., to disclose the results of opening the package for the case. When the occurrence of a serious adverse event is recognized, all serious adverse events will be promptly reported to the hospital director, regardless of whether there is a causal relationship with the research

## Serious adverse event reporting

　A "serious adverse event" is defined as any unfavorable medical event, regardless of dose, that meets the following criteria

(1) Lethal events

(2) Life threatening

(3) Events that require hospitalization for treatment

(4) Permanent or significant disability or malfunction

(5) Those that cause congenital anomalies in the offspring

If the principal investigator recognizes the occurrence of a serious adverse event while conducting an invasive study, the principal investigator shall promptly report all serious adverse events to the hospital director (Clinical Trial Review Committee in the case of Osaka City University), regardless of whether or not there is a causal relationship with the study, and shall also report to the responsible physician of the other medical institution if a causal relationship between the study and the serious adverse event cannot be ruled out in a multicenter study.

## Other adverse events

Other adverse events should be described in the case report form according to the procedures described in "8. Observation and examination items (4) Confirmation of adverse events and side effects.

# Termination, discontinuation, or suspension of the study

## Termination of the study

At the end of the study at each institution, the principal investigator shall promptly submit a study termination report to the hospital director. If the study is to be conducted at multiple institutions, a termination report will also be submitted to the principal investigator.

## Discontinuation, or suspension of the study

　The principal investigator will consider whether to continue the study if any of the following apply.

1) When significant information regarding the quality, safety, or efficacy of the test food is obtained.

2) When it is judged to be difficult to recruit subjects and to achieve the planned number of cases.

3) When the Review Committee instructs changes to the implementation plan, etc., and it is judged to be difficult to accept the changes.

If the Review Committee recommends or directs that the study be stopped, the study will be stopped. In the case of a multi-center study, the principal investigator or the committee specified in the study protocol will review the above items and consider whether to continue the study. When a decision is made to discontinue or suspend a study, the decision shall be promptly reported to the hospital director in writing with the reasons for the decision.

# Evaluation items

## Primary endpoints

　The primary endpoint of this study is the change in disease activity DAS28-ESR at 24 weeks after the start of the test food intake.

【Evidence of setting】

　In this study, we will investigate the suppressive effect of Brazilian propolis on the disease activity of RA. The above item of disease activity is the gold standard not only for ACR/EULAR but also for the assessment of disease activity in RA worldwide.

## Secondary endpoints

1. DAS28-CRP, SDAI and CDAI at week 12, 24 and 36.
2. QOL evaluated by the change of the score by SF-36 at week 24.
3. The change of ADL evaluated by mHAQ at week 12, 24 and 36.
4. The change of sonographic total scale of hand and foot joint at week 12, 34 and 36.
5. Adverse events requiring discontinuation of the test food up to 24 weeks after starting ingestion.
6. Severe adverse events up to 36 weeks after starting ingestion.
7. All adverse events up to 36 weeks after starting ingestion.

【Evidence of setting】

1） Other methods of assessing disease activity other than the DAS28-ESR, each of which has its own advantages and disadvantages, should also be used.

2) As a general QOL assessment tool for subjects, the SF-36 has been reported in numerous articles due to its simplicity and reliability. We will evaluate the effect of QOL improvement associated with suppression of disease activity.

3) It is the gold standard for the assessment of ADL in RA patients not only in ACR/EULAR but also worldwide. We will evaluate the improvement of ADL with the suppression of disease activity.

4) Obtain a more objective assessment because disease activity assessment includes many subjective items.

5-7) To evaluate the safety of test foods.

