## Study method

　Eighty female RA patients with moderate disease activity according to the DAS28-ESR will be randomly divided into 40 patients in the propolis group (P group) and 40 patients in the placebo group (C group). P group takes 5 test tablets containing Brazilian propolis (508.5 mg as propolis) per day, and C group takes 5 placebo tablets without Brazilian propolis per day. The DAS28-ESR will be compared in both groups at the time of intervention and after 24 weeks. This will be followed up with a 12-week post-intervention observation period.

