## Dosage and administration of the test food, and duration of administration

　P Group will receive 5 test tablets containing Brazilian propolis daily, and C Group will receive 5 placebo tablets daily. No time of administration is specified. The test food will be provided in sachet packages of five tablets each, with the intention of ingesting five tablets at a time, but it will be acceptable for study participants to ingest them in divided portions. If patients do not take 5 tablets in a day, do not take them the next day and return the whole sachet at next visit. No more than five tablets per day were to be taken. The entire sachet will be collected at each visit, so any leftovers should be checked and recorded at this time. The administration period should be 24 weeks.

［Evidence for setting the dose and duration of administration］

　The dose of the test food containing Brazilian propolis used in this study was 5 tablets (508.5 mg of Brazilian propolis extract powder), which is the midpoint of the 4-6 tablets per day set as the standard dose by Yamada Bee Company, Inc.

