## Secondary analysis

Analyses of secondary endpoints will be conducted to provide supplementary insights to the primary analyses of the study. The secondary endpoints will be analyzed with exploratory intent and will not be adjusted for multiplicity. 1) DAS28-CRP, SDAI, CDAI, at 12, 24, and 36 weeks after intake 2) QOL at 24 weeks after intake (SF-36), 3) ADL at 12, 24, and 36 weeks after intake: mHAQ 4) sonographic examination of joints (scale change) at 12, 24, and 36 weeks after the start of intake will be analyzed in the same way as the primary endpoint. A frequency table will be prepared for each administration group regarding the occurrence of adverse events. In the case of serious adverse events, Kaplan-Meier curves will be generated for survival analysis until the occurrence of the event, and the groups will be compared using Cox proportional hazards model with DAS28-ESR at 0 week as a covariate. For quantitative data on clinical laboratories, summary statistics will be calculated for each time point and the amount of change from before the start of the test food administration for each dose group, and a scatter plot will be created. For other qualitative data, a frequency table should be created for each administration group.

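### Severe and all adverse events are counted in one 36-week window to judge test-food safety, although intake ends at week 24 and no split by intake period is stated

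*Protocol*

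**What the plan says.** **Exposure.** Protocol section 7.4: "The administration period should be 24 weeks". The study method in the outline adds: "This will be followed up with a 12-week post-intervention observation period". Weeks 24 to 36 are therefore off the test food.

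**Safety endpoints (section 12.2).**
- Endpoint 5: "Adverse events requiring discontinuation of the test food up to 24 weeks after starting ingestion".
- Endpoint 6: "Severe adverse events up to 36 weeks after starting ingestion".
- Endpoint 7: "All adverse events up to 36 weeks after starting ingestion".

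The rationale below the list gives one purpose for all three, the safety of the test food.

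**Analysis (section 14.3).** "A frequency table will be prepared for each administration group regarding the occurrence of adverse events". For serious events there are also Kaplan-Meier curves and a Cox model adjusted for week-0 DAS28-ESR. Neither the table nor the model is divided by intake period.

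**Definition and collection.** Section 10.1 describes an adverse event as "any unfavorable or unintended sign, symptom, or illness that occurs when a test food is administered", whether or not it is causally related. The section 8 timetable schedules adverse-event observation at the post-observation visit, and its footnote defines adverse events without reference to administration. Section 8 also has the time of occurrence and the relationship to the test food recorded for each event.

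**The concern.** Endpoints 6 and 7 are meant to show whether taking the food causes harm, but a third of the time they cover is time when nobody takes it. Events from that period enter both arms' counts. If the arms do not differ after stopping, those events pull the comparison towards no difference, so a real on-intake excess looks smaller than it is. If the arms do differ after stopping, for whatever reason, the difference is credited to the food as though it arose during intake. One count over 36 weeks cannot tell these cases apart.

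Endpoint 5 is limited to the intake period, so the protocol does recognise an intake-only window. But endpoint 5 covers only events that led to stopping the food. No stated comparison covers all events, or all severe events, during intake.

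The wording in 10.1 adds a second difficulty. Read literally, it leaves out events that begin after week 24, which sections 8 and 12.2 ask for. The definition and the endpoint window should agree.

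**Working it through.** The protocol gives no numerical figure for adverse events, so there is none to reproduce here. Its one design calculation, 39 per group for DAS28-ESR at week 24, reproduces (2 × (0.78 × (1.960 + 0.842) / 0.5)² = 38.2, rounded up to 39) and does not bear on this point.

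**Inputs from the protocol**
- Intake period: 24 weeks (section 7.4).
- Observation after intake: 12 weeks (outline, study method).
- Window for endpoints 6 and 7: 0 to 36 weeks (section 12.2).

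**Assumptions, not in the protocol**
- A constant background event rate, the same in both arms.
- A ratio RR of propolis to placebo event rates during intake, taken as 1.5, 2 or 3.
- A ratio of 1 after stopping.

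**Step 1: share of the window off the food.** 12 / 36 = 0.333, or 33%.

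**Step 2: ratio seen over the pooled window.** Pooled ratio = (24 × RR + 12 × 1) / 36.

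| On-intake ratio | Calculation | Ratio over 36 weeks |
| --- | --- | --- |
| 1.5 | (36 + 12) / 36 | 1.33 |
| 2 | (48 + 12) / 36 | 1.67 |
| 3 | (72 + 12) / 36 | 2.33 |

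**Step 3: the same check for a table of patients with at least one event.** A frequency table may count patients rather than events. Let p be the assumed placebo risk over 24 weeks, with constant hazards. For a rate ratio of 2, the 24-week risk ratio is [1 − (1 − p)²] / p. The 36-week risk ratio is [1 − (1 − p)^2.5] / [1 − (1 − p)^1.5], where the exponents are (2 × 24 + 12) / 24 = 2.5 and 36 / 24 = 1.5.

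| Assumed placebo risk at 24 weeks | Risk ratio, weeks 0–24 | Risk ratio, weeks 0–36 |
| --- | --- | --- |
| 10% | 1.90 | 1.58 |
| 20% | 1.80 | 1.50 |
| 40% | 1.60 | 1.35 |

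The dilution is of similar size on either scale.

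**Step 4: dependence on the third assumption.** With a ratio r after stopping, the pooled ratio is (24 × RR + 12 × r) / 36. If r equals RR, there is no dilution. If RR = 1 and r = 2, the pooled ratio is (24 + 24) / 36 = 1.33, an apparent excess with none during intake. The direction of the distortion therefore depends on what happens after week 24, which the single window does not show.

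**Step 5: the serious-event model.** A Cox model without a term for period gives one hazard ratio across on-food and off-food time, so it averages the two periods in the same way. No figure is given, because the weights depend on when events occur.

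**Step 6: the definitions side by side.** Section 10.1 ties the event to administration, which ends at week 24. The section 8 timetable and footnote, and endpoints 6 and 7, run to week 36 without that tie. They cannot all be applied literally to an event that begins in week 30.

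**The case against.** Following events after the last intake is ordinary and sound practice. Nothing in section 14.3 forbids rows by period, and table layout is commonly left to a statistical analysis plan, which is not shown here. Onset times are recorded, so the split could be made at any time. The ratios above are assumptions, and worsening after stopping may itself be useful safety information. All of this stands, and it is why the point is minor. What remains is that the protocol itself fixes the single window in endpoints 6 and 7 and gives food safety as their purpose, and that the 10.1 wording is a protocol matter.

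Three stronger readings are tempting, and the documents do not support them.

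- *That week-36 efficacy is mixed with week 24.* A reader might infer this because section 14.3 says the secondary measures "at 12, 24, and 36 weeks after the start of intake will be analyzed in the same way as the primary endpoint". But the primary endpoint is week 24 alone, the DAS28-ESR mixed model uses only weeks 12 and 24, and week 36 is a separate time point. The same model there gives a valid randomised comparison 12 weeks after stopping. Carrying on-food values forward by LOCF would blur it, but section 14.1 ties LOCF to the main analysis, so its use at week 36 is only an inference.
- *That a test of change from week 24 to week 36 is required.* The protocol states no withdrawal objective. The disease-activity indices, mHAQ and ultrasound are analysed at weeks 12, 24 and 36, so an effect present at 24 and absent at 36 would be visible.
- *That sites will record different events because of 10.1.* Section 10.3 sends other adverse events to the section 8 procedure, the timetable marks the post-observation visit, and endpoint 7 states 36 weeks. Together these largely settle the window. The 10.1 wording is loose, but divergent recording is not shown.

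**Conclusion.** The point holds for the safety endpoints only. Endpoints 6 and 7 combine 24 weeks on the food with 12 weeks off it, and no split is stated for either the frequency table or the serious-event Cox model. Under a constant background rate and no effect after stopping, an on-intake rate ratio of 2 would be shown as 1.67 (1.33 to 2.33 for true ratios of 1.5 to 3). Under other assumptions about the period after stopping, the distortion could vanish or reverse. Section 10.1 does not fit the week-36 collection in sections 8 and 12.2, and these passages must be reconciled.

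Severity is minor. Section 14.3 calls the secondary endpoints exploratory, and neither the primary result nor the sample size is affected.

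**What to change.** 1. Keep adverse-event follow-up to week 36.
2. In sections 12.2 and 14.3, state that endpoints 6 and 7 are tabulated by onset in two periods: from first to last intake, and from last intake to week 36. Name the first as the food-safety comparison. For patients who stop early, divide at their own last intake rather than at week 24.
3. For serious events, also give the Cox comparison restricted to the intake period.
4. Align the adverse-event wording in 10.1 with sections 8 and 12.2 so that it covers the whole collection period.
5. Optionally, label the week-36 efficacy results as off-intake. No further efficacy analysis is needed for this point.

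The change is wording in 10.1, 12.2 and 14.3. Section 8 already records the time of occurrence, and section 9 the date of discontinuation. The cost is smaller counts in each table, which matters with 40 patients per group. A total column over 36 weeks can stand beside the two periods.
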